**Figure 2 F2:**
[figure not shown]
Flowchart of PEACH study intervention process.

### The intervention

Practice Nurses in practices randomised to intervention group undertake a two-day training program in telephone coaching for diabetes using the adapted COACH manual. The telephone coach intervention addresses lifestyle and pharmacological management of hyperglycaemia, and specifically focuses on achieving HbA1c of less than 7% as the goal of treatment. Goals of treatment for the secondary outcomes are also given in table 1. The treatment algorithm given in table 1 is adapted from the Steno-2 Study [30] and is virtually the same as previously used in management of cardiovascular risk factors in patients with coronary heart disease [21,22].

**Table 1 T1:** Treatment algorithm for PEACH study participants adapted from the Steno-2 Study [30].

**Risk Factor**	**Treatment Goal**
HbA1c	<7%
Total cholesterol	<4.0 mmol/L
Blood pressure	<130 mmHg for systolic and <80 mmHg for diastolic
Physical activity	Light to moderate activity for 30 minutes or more on most or all days a week
Smoking	Smoking cessation
Saturated fat	<8% of total daily energy intake
Aspirin	Low dose of aspirin

The COACH Program includes a letter welcoming the patient to the COACH Program and providing written information about coaching sessions. Patients also receive a one-page chart of risk factor targets and a folder with the name and contact details of their Practice Nurse "coach". This folder is designed to store all future COACH Program correspondence. In addition, the Practice Nurse coach places the same one-page chart of risk factor targets and notification of details of patient enrolment in the patient's file for when they next see their GP. The 'Coaching Program' involves five coaching telephone calls at six weekly intervals in the first 6 months, two coaching telephone calls at two monthly intervals between 6–12 months, a face to face coaching session at 12 months and one coaching call at 15 months. Intervention group patients continue to receive usual General Practice care from their GP which can include referral to diabetes educators, dietitians and diabetes specialists that form part of standard diabetes care for patients of that practice.

Patients are coached according to the COACH Model, a process of continuous quality improvement which involves coaching the patient to go to their doctor and obtain measurement of their risk factors and to be informed of the results of these measurements, education regarding risk factor targets, negotiation of a plan of action to achieve the target that includes focus on both medication and lifestyle and subsequent monitoring of progress by the patients toward the achievement of the target level. This quality improvement cycle is a key feature of the COACH Program – each coaching session is used as the foundation for the next coaching session. There is no pre-set time frame for coaching sessions. The length of the calls is determined by the length of time the "coach" needs to establish a plan of action with the patient to be achieved by the next coaching session. Patients are able to contact their Practice Nurse coach between coaching sessions, for questions and further information as required. A specific software package designed for the COACH program is used in conjunction with the telephone coaching sessions to generate written reports for the patient summarising each verbal coaching session, and to inform the "coach" for the next session. Reports are posted to the patients and a copy is placed in each patient's file. Practice Nurses are paid for their training time and for their coaching time.

### Sample size calculations

The unit of randomisation in this RCT is the general practice. A total of 546 patients (13 patients per practice) from 42 general practices will be required (273 in each arm) to show an absolute 0.5% or greater reduction in mean HbA1c in the intervention arm compared with usual GP care group. The sample size allows for a design effect of 1.4 due to the increased variance of recruiting patients within practices and an attrition rate of 20% over 18 months and overall attrition rate of 30% over 3 years in anticipation of an extension of the study for another 18 months pending funding. Calculations are based on a two sample t-test for means, with a standard deviation of 1.44 (this is based on results from a previous diabetes project in General Practice in the region involving 1,088 diabetes patients), 80% power and significance level at 5% for a two sided test. The design effect is based on a conservative estimate of the intra-cluster correlation (ICC) for HbA1c of 0.05.

### Data collection, monitoring and analysis

Descriptive statistics will be used to summarise general practice, practice nurse and patient factors for the two study groups and to check for any imbalance in baseline variables between control and intervention group. GP practice will be set as the primary sampling unit. Outcomes between study groups will be compared to assess the effect of the intervention. Primary and secondary outcomes will be analysed using marginal models using Generalised Estimating Equations with information sandwich (robust) standard errors to allow for the effect of clustering of patients within general practices. Analysis will be 'intention to treat' and where appropriate regression analysis will be adjusted for baseline outcome measure and any baseline variables that are imbalanced between the two study groups. Sensitivity analysis will examine the effect of loss to follow-up on the intervention effect. Exploratory analyses are also planned to examine the effect of explanatory factors (e.g. socio-demographic factors such as education level or employment status of patients) on the outcome.

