### Inclusion and exclusion criteria

Practices with a practice nurse are eligible to participate, and must achieve a minimum recruitment of five patients to the study to continue. Patients with T2D are eligible to participate if they are >18 years, their most recent HbA1c is greater than 7.5% and they are receiving care from a General Practice that employs a Practice Nurse and is located in one of the participating Divisions of General Practice. Patients are excluded if they are not contactable by telephone, have a complex debilitating coexisting medical condition (e.g. mental illness, end-stage cancer), or do not provide signed consent. Patients from non-English speaking backgrounds are eligible and are able to utilise a free telephone interpreting service to find out more information about the study and throughout the data collection and intervention phases.

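### The GEE analysis of 42 practices names robust standard errors without a small-sample correction; if none is used, the two-sided 5% test of HbA1c runs at about 6.1–6.6%, and higher with practice-level covariates

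*Protocol article*

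**What the plan says.** Under Data collection, monitoring and analysis, the protocol article makes the practice the primary sampling unit and analyses primary and secondary outcomes by "marginal models using Generalised Estimating Equations with information sandwich (robust) standard errors to allow for the effect of clustering". Where appropriate, the regression adjusts for the baseline value of the outcome and for whatever baseline variables turn out to be imbalanced. The same paragraph says that practice, practice nurse and patient factors will be examined for imbalance. The number of adjustment variables is left open.

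Under Sample size calculations it states: "The unit of randomisation in this RCT is the general practice", and "A total of 546 patients (13 patients per practice) from 42 general practices will be required (273 in each arm". The test criteria are "80% power and significance level at 5% for a two sided test".

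The article does not mention a finite-sample correction, a t or normal reference, or a working correlation.

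**The concern.** The robust sandwich variance is justified as the number of clusters grows. The number of patients does not help. With 21 practices per arm, the standard form is biased downward, because it is built from residuals that the fitted model has already pulled towards zero. A normal critical value then ignores the uncertainty in a variance estimated from about 40 degrees of freedom. Both faults act in the same direction: P values too small and intervals too short.

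Each practice-level covariate uses up between-practice information and makes this worse. The adjustment rule allows such covariates without a cap. What is at stake is whether the stated 5% level holds for the primary HbA1c comparison.

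**Working it through.** **Inputs from the article.** 42 practices (21 per arm if split equally), 13 patients per practice, difference 0.5 percentage points of HbA1c, SD 1.44, ICC 0.05, design effect 1.4, attrition 20% at 18 months and 30% over 3 years, 80% power, two-sided 5%.

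**The plan's own sample size.**
- Patients per arm without clustering: 2 × (1.960 + 0.842)² × 1.44² / 0.5² = 130.2, so 131.
- With the design effect: 131 × 1.4 = 183.4, so 184.
- With 30% attrition: 184 / 0.7 = 262.9, so 263.
- In practices of 13: 263 / 13 = 20.2, so 21 practices, and 21 × 13 = 273 per arm, 546 in total.
- The design effect fits the cluster size after 30% attrition: 1 + (9.1 − 1) × 0.05 = 1.405.

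The stated 546 is reproduced and is not in question.

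**Closed form for the type I error** (21 equal practices per arm, no covariates, normal practice means).
- The standard sandwich variance is too small by the factor 20/21, so the standard error is too small by √(20/21) = 0.976.
- Comparing the statistic with 1.960 therefore amounts to comparing a correct t statistic on 40 df with 1.960 × 0.976 = 1.913.
- True two-sided error: 2 × P(t₄₀ > 1.913) = 6.3%.
- Interval length relative to the correct one: 1.913 / 2.021 = 0.946, about 5% too short.

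**Null simulations.** Gaussian outcome, exchangeable GEE, 42 practices, ICC 0.05 unless stated, standard sandwich with normal reference. Most settings had 10,000–15,000 runs (Monte Carlo SE about 0.2 points).

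| Covariates in the model | Rejection at nominal 5% |
|---|---|
| None | 6.3–6.4% (6.1% at ICC 0.01, 6.6% at ICC 0.10) |
| Baseline HbA1c | 6.1–6.6% |
| Baseline plus two patient-level | 6.7% |
| Baseline plus two practice-level | about 7–7.5% |
| Baseline plus several, including further practice-level | about 8–9% |

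A smaller set of 4,000 runs per setting (Monte Carlo SE about 0.4 points) gave 6.4–6.8%, 7.7% and 9.2% for baseline only, two practice-level covariates and five. This agrees within simulation error.

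**Does the remedy work?**
- Kauermann-Carroll type correction with a t reference: 4.7–5.7% across settings from baseline only to five practice-level covariates.
- Leave-one-cluster-out type correction with t on 40 df: about 4.2–4.9% (no covariates or baseline only).
- A t reference alone, with the standard sandwich: about 5.3–6.0% without practice-level covariates, but 6.5–7.9% with them. The variance correction is therefore needed as well.

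**Power after the fix** (unadjusted, equal practice sizes, t on 40 df). SE = 1.44 × √(2 × DE / (21 × m)), where m is completers per practice and DE = 1 + (m − 1) × 0.05.
- 20% attrition: m = 10.4, DE = 1.47, SE = 1.44 × √(2.94 / 218.4) = 0.167, 0.5 / 0.167 = 2.99, power 83%.
- 30% attrition: m = 9.1, DE = 1.405, SE = 1.44 × √(2.81 / 191.1) = 0.175, 0.5 / 0.1746 = 2.86, power 79.8%.

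**The case against.** The strongest reply is that silence is being read as a decision. The article names a class of standard error. The corrected estimators recommended here are themselves sandwich estimators, so the sentence as written does not exclude them. Reference distribution and finite-sample correction are details that a condensed article often leaves to a fuller document. This stands to the extent that a reader might infer that uncorrected standard errors are planned, or that the real error rate is known to be well above 5%. The text supports neither. What remains is that the article does specify the type of standard error. Taken in its ordinary sense, that wording means the standard estimator, since the corrected versions have their own names.

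The reply on size also stands. The only covariate that the article names specifically is the baseline outcome, and there the error is about 6.1–6.6%. Rates of 8–9% need several practice-level covariates. Their number, the prevalence of the stratum factors and the spread of practice sizes are not in the article, nor does it say that the stratification factors enter the model.

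Two further inferences should not be drawn. The rule that practices "must achieve a minimum recruitment of five patients to the study to continue" suggests unequal practice sizes, but it does not support this point: in the set of runs that compared them directly, unequal sizes gave 6.4% and equal sizes 6.8%, which simulation error cannot separate. And the figures are for a continuous outcome with the HbA1c ICC; the size of the effect for binary secondary outcomes, such as smoking, has not been shown.

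**Conclusion.** The point holds in conditional form. If the named standard errors are computed in the standard way with a normal reference, the primary test misses its 5% level by roughly 1.1–1.6 percentage points in the baseline-adjusted analysis. The excess is about 2–2.5 points with two practice-level covariates and about 3–4 points with several.

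This rests on 42 practices split equally, normally distributed outcomes and, for the figures above 6.6%, assumed covariate numbers. The direction is not in doubt, and the simplest case follows from the closed form without simulation. It is a modest anti-conservative error that is cheap to prevent before analysis. It is not a fault in the choice of GEE or in the sample size.

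**What to change.** Keep GEE with the practice as the cluster. State that inference will use a small-sample-corrected sandwich variance (Kauermann-Carroll or Fay-Graubard), and that the statistic will be referred to a t distribution with df equal to the number of practices minus the number of practice-level parameters. That is 42 − 2 = 40 before covariates, and one fewer for each practice-level covariate. If the full protocol or analysis plan already says this, it only needs to be confirmed.

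The cost is one sentence and a software option. Without covariates, intervals become about 6% wider than those from the standard sandwich with a normal reference (2.021 / 1.913 = 1.057). With equal practice sizes, power stays above the planned 80% at 18 months and is 79.8% at the 30% attrition allowed for the possible extension.

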**Methods/design:**

In a cluster randomised controlled trial, general practices employing Practice Nurses (PNs) are randomly allocated to an intervention or control group. We aim to recruit 546 patients with poorly controlled T2D (HbA1c >7.5%) from 42 General Practices that employ PNs in Melbourne, Australia. PNs from General Practices allocated to the intervention group will be trained in diabetes telephone coaching focusing on biochemical targets addressing both patient self-management and engaging patients to work with their General Practitioners (GPs) to intensify pharmacological treatment according to the study clinical protocol. Patients of intervention group practices will receive 8 telephone coaching sessions and one face-to-face coaching session from existing PNs over 18 months plus usual care and outcomes will be compared to the control group, who will only receive only usual care from their GPs. The primary outcome is HbA1c levels and secondary outcomes include cardiovascular disease risk factors, behavioral risk factors and process of care measures.

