### Baseline assessment

Baseline assessment is conducted by the Practice Nurse and takes approximately one hour to complete. Patient written consent is obtained prior to undertaking baseline assessment. Baseline assessment includes data collected by the Practice Nurse at interview (patient knowledge of appropriate testing and goals for risk factors, smoking status, current exercise levels and a dietary history using a validated food frequency questionnaire [24]), from the patient file (treatment, test frequency and most recent pathology results), and patient self report data (diabetes self efficacy scale [25], the diabetes support scale[26], a quality of life scale [27] and a measure of depression [28]). Patients are instructed to arrange baseline testing for HbA1c, total and HDL cholesterol, and renal function at their usual local pathology laboratory. Follow up tests will all be done at the patients' usual pathology laboratory. All participating laboratories use HbA1c assay methods that are DCCT aligned [29] and participate in a regional quality assurance program for HbA1c assays.

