### Outcome assessment

Data collected at baseline, including primary and secondary outcome measures, will be collected again at 12 and 18 months post-intervention for both the intervention and control groups. Study team nurses blinded to the group allocation of participants will collect 12 month and 18 month follow up data by face-to-face interview with the patient. We will also access administrative data sets in relation to health service use and cost.

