### Randomisation

General Practices are randomised to either the intervention or control group after all baseline assessments are completed (figure 2). Block randomisation with random block sizes, stratified according to the organisational and financial arrangements of the general practices (fee-for-service private practice or state government funded community health centre status) and whether they are participating in the National Primary Care Collaboratives Program (A national pilot quality improvement program aimed at improving quality of chronic disease care and currently involving approximately 7% of general practices) is used to allocate practices to study groups. The allocation sequence is computer generated by the statistician from the research team, blinded to the identity of the general practices. Following randomisation, practices are informed by a letter from the Chief Investigator of whether their practice will be in the intervention or control group.

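### The covariate rule lets observed baseline imbalance shape the primary HbA1c model, and does not fix adjustment for baseline HbA1c or the randomisation strata

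*Protocol article*

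**What the plan says.** All statements are in the Protocol article.

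- **Data collection, monitoring and analysis.** Practice, nurse and patient factors are summarised by arm "to check for any imbalance in baseline variables between control and intervention group". Primary and secondary outcomes are then analysed with "marginal models using Generalised Estimating Equations with information sandwich (robust) standard errors". The covariate rule follows: "where appropriate regression analysis will be adjusted for baseline outcome measure and any baseline variables that are imbalanced between the two study groups". The section does not define imbalance, list candidate variables, say when adjustment is appropriate, or tie the choice to a time before outcomes are known.
- **Randomisation.** "General Practices are randomised to either the intervention or control group after all baseline assessments are completed". Allocation is stratified by two practice factors: funding arrangement and participation in a national quality programme. The covariate rule mentions neither.
- **Baseline assessment.** "Patients are instructed to arrange baseline testing for HbA1c, total and HDL cholesterol, and renal function". The primary outcome is therefore requested from every patient before allocation. Eligibility also depends on a recent HbA1c above 7.5%.
- **Outcome assessment.** The baseline measures "will be collected again at 12 and 18 months post-intervention for both the intervention and control groups".

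**The concern.** Patients are enrolled and measured before their practice is allocated. The usual reason in a cluster trial for suspecting systematic imbalance, recruitment that differs by arm after allocation, therefore does not apply. Among randomised patients any imbalance is chance, and its size says nothing about whether the variable predicts HbA1c. A rule driven by imbalance can admit practice or nurse characteristics with no prognostic value, and each practice-level term uses one of about 40 between-practice degrees of freedom (42 practices less 2 arms). The rule also stops short of requiring the most obvious prognostic covariate, baseline HbA1c, and the factors used to stratify.

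Two things are at stake. Precision that the trial has already collected may be given up. The content of the primary model is also left to judgement at a point when the arms have been compared.

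**Working it through.** **Inputs from Sample size calculations:** difference 0.5% HbA1c; SD 1.44; 5% two-sided; 80% power; ICC 0.05; design effect 1.4; attrition 20% at 18 months and 30% at 3 years; 42 practices of 13, 273 per arm.

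**Assumed, because the article does not give it:** the correlation r between baseline and follow-up HbA1c, taken as 0.3, 0.5 or 0.7 at both patient and practice level. Recruiting only patients above 7.5% narrows the baseline range, so the lower values deserve weight.

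**1. The plan's own figure.** n per arm = 2 × (1.44 × (1.960 + 0.842) / 0.5)² = 130.2, rounded up to 131. Then 131 × 1.4 / (1 − 0.30) = 262. Since 262 / 13 = 20.2, 21 practices per arm are needed: 21 × 13 = 273 per arm, 546 in total. The stated figure reproduces. It rests on an unadjusted two-sample t-test.

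**2. Unadjusted precision at 18 months.**
- Patients left per practice: 13 × 0.8 = 10.4. Design effect: 1 + (10.4 − 1) × 0.05 = 1.47.
- Effective n per arm: 273 × 0.8 / 1.47 = 148.6.
- SE = 1.44 × √(2 / 148.6) = 0.167. Power for 0.5% is 84.9%.

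**3. With baseline HbA1c always in the model.** Residual SD = 1.44 × √(1 − r²), so the variance falls by r².

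| r | variance reduction | SE | power |
|---|---|---|---|
| 0.3 | 9% | 0.159 | 88.0% |
| 0.5 | 25% | 0.145 | 93.3% |
| 0.7 | 49% | 0.119 | 98.7% |

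**4. What an imbalance trigger would do if it also governed baseline HbA1c.** Practice means were simulated: 21 practices per arm, 10 patients each, ICC 0.05, 100,000 runs. Imbalance was taken as P < 0.05, a threshold that the article does not state.

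| r | power, always adjusted | power, adjusted only if imbalanced | type I error, adjusted only if imbalanced |
|---|---|---|---|
| 0.3 | 84.7% | 82.4% | 4.6% |
| 0.5 | 90.7% | 83.1% | 4.3% |
| 0.7 | 97.9% | 84.0% | 3.6% |

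Power is slightly below step 3 because practice means were tested against a t distribution.

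**5. How often chance would flag something.** If 15 to 20 independent variables were each tested at 5%, the probability of at least one flag would be 1 − 0.95¹⁵ = 54% to 1 − 0.95²⁰ = 64%. The test, the threshold, the count and the independence are all assumptions. The article speaks only of descriptive statistics.

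**The case against.** **Baseline HbA1c may always be in the model.** Grammatically, the words about imbalance qualify the other baseline variables and not the baseline outcome measure, which is listed separately. The qualifier *where appropriate* covers outcomes of mixed type, including process-of-care measures for which a baseline value may not apply. A reader might infer that HbA1c is adjusted only if imbalanced; the text does not say so. This objection stands as a limit on size: on the more natural reading the losses in steps 3 and 4 disappear. It does not rescue the wording, which never makes the adjustment unconditional.

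**The trigger is baseline data.** A reader might infer that the model is chosen on outcome results and that type I error is inflated. The rule as written points to baseline comparisons, and in step 4 it is conservative. Reporting whichever of the adjusted and unadjusted models is significant would give 6.3%, 7.3% or 8.2% in the same simulation, but the article does not propose that. What remains is that nothing in the text rules it out.

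**Adjusting for an imbalanced prognostic variable has a purpose.** In the runs under no effect where baseline HbA1c was imbalanced, the unadjusted test rejected in 10.4%, 18.8% and 32.1% (r = 0.3, 0.5, 0.7). This is true, but adjustment fixed in advance gives the same protection without inspecting the arms.

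**Covariate detail belongs in an analysis plan.** A missing list would be no fault in an article. Here, however, the article states a selection rule, and an analysis plan faithful to it would carry the rule forward.

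**Conclusion.** The point holds as a poorly chosen rule with avoidable costs. It does not show invalid inference.

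On any reading, selecting covariates by chance imbalance is a weak basis for the primary model and leaves discretion open after the arms are compared, and the strata are not named. On the less favourable reading, in which baseline HbA1c can be omitted, the trial forgoes a variance reduction of 9% to 49%. That range rests entirely on the assumed correlation of 0.3 to 0.7.

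A reader might also infer that the trial is underpowered. It is not: 546 was derived without adjustment, and unadjusted power at 18 months is 84.9% under the article's own inputs. The 54% to 64% in step 5 illustrates how a conventional screen would behave and is not a property of the stated plan.

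**What to change.** Replace the covariate sentence with a fixed specification:

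- The primary model contains arm, baseline HbA1c and the two randomisation strata. For other outcomes, use the baseline value of that outcome where it was measured.
- Any further covariates are chosen because they are expected to predict the outcome, and are named before outcome data are seen.
- Adjustment for variables found imbalanced is reported as a labelled sensitivity analysis and does not replace the primary result.

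The strata can enter as two main effects, which takes two between-practice degrees of freedom (40 to 38). The article puts national participation in the quality programme at about 7% of practices. If the sample matched that, about 3 of 42 practices would participate (0.07 × 42 = 2.9), so the text should say in advance what happens if a level is empty.

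The cost is rewording only. Baseline HbA1c is already requested from every patient, the strata are known at allocation, and the sample size does not change.
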